### Data collection, management and monitoring

#### Questionnaire

During the baseline and endline surveys we will collect all data via a digital questionnaire. A Microsoft Word version of the questionnaire is available in the Supplementary materials (see *Survey questionnaire* in Supplementary file 2). The questionnaire will record basic trial related data, such as the date and time, cluster and village identifier codes, and participant consent. It will also record a range of data on participants’ socio-demographic characteristics, such as their age, sex, education levels and animal ownership details. It will also record participants’ responses to the questions that will be used to generate the primary and secondary outcomes. Our endline survey questionnaire will also contain a series of questions about attendance and/or awareness of the CDs (both among participants and their family/friends etc.) to allow some of our planned subgroup analyses. The questionnaire was developed into an Android-based app using the commercial Survey CTO platform^3^, which in turn is based on the Open Data Kit^4^ platform. In the field the questionnaire will be completed by the data collectors via tablets running the Android operating system.

#### Data collection team

All data will be collected by two field teams, one created for the baseline survey and one created for the endline survey. Each team will consist of five or six enumerators (depending on how efficient the baseline team is), who will be chosen based on having experience of collecting data health survey data in these settings using tablets (we expect these individuals to be largely/entirely made-up of MSc students from Dhaka University studying health related degrees). The team will undergo a 5-day training program, delivered by members of the Bangladeshi research team and a member of the data collection app team. The training will cover the goals of the study, its design, the survey locations, the household and participant sampling methods, the questionnaire and data collection processes.

We will check their understanding and ability to collect data using a mock test on the survey questionnaire. This will allow us to address any weaknesses in their performance and any final issues identified with delivering the questionnaire. They will then practice sampling households and collecting data from a small number of community members in a similar field setting to the study sites, but in a site that will not form part of the study. There will then be a final day where the data collectors can discuss their learning from the practice field trip and solve any remaining issues.

#### Data quality

In the questionnaire app we will automate all required skips and build in a range of data formatting and sense checks to minimize errors when collecting data. The Bangladeshi research team, who are responsible for the running of the trial and data collection, will also make use of the Survey CTO platform’s ability to live stream audio of interviews to monitor a sample of initial interviews with each data collector. This will allow them to provide real-time and post-interview feedback to further improve the consistency with which interviews are conducted.

#### Data management

All data collected in the field will be transferred remotely via the internet to a secure server, from where it will be downloaded for processing. We will then carry out a standard series of data quality, accuracy and sense checks for each variable before creating a final dataset for analysis.

#### Trial monitoring and harms

The study sponsor is the University of Leeds (UK). We have created a trial steering group consisting of three senior researchers at the University of Leeds with relevant experience, who are within the School of Medicine but are not part of the project. Their remit is to provide advice aimed at the successful conduct of the trial, based on regular updates from the trail team. However, they will not look at any trial outcome data (although we will report monitoring data on the implementation of the interventions and on the progress of trial data collection). It was decided not to create a data monitoring committee because the design of the trial will involve a baseline and an endline cross-sectional survey. Therefore, there is no collection of trial outcome data throughout the intervention period, and so there is no opportunity to conduct interim analyses that may be used to stop the trial early. It was also not feasible to collect any data on potential harms.

### Trial schedule

Figure 1 illustrates the trial schedule. For logistical reasons, we will start by conducting the baseline survey in the clusters of one subdistrict before starting the baseline survey in the clusters of a second subdistrict approximately two-weeks later, and so on for the remaining subdistricts, such that all these activities will be collectively staggered by approximately 2 weeks between the subdistricts.

### Statistical analyses

Prior to database lock we will produce a statistical analysis plan. Therefore, below we just summarize the key details of the approaches we will use.

#### General principles

##### Participant and cluster characteristics

We will describe the cluster-level and individual-level distribution of relevant participant characteristics (e.g., age, sex, education level) across all cluster at baseline and endline, using standard descriptive statistics, to help inform judgments about the generalisability and transportability of the treatment effects. Using the same types of statistics, we will also describe the cluster-level and individual-level distribution of these characteristics across the clusters within each treatment group, to enable judgments about the balance of these characteristics between the treatment groups (and therefore the success of the randomization process).

##### Outcome treatment effects

When estimating treatment effects on our trial outcomes we will include all clusters and participants and analyze them according to their original cluster-randomized allocation, unless explained otherwise. This is to ensure that treatment effect estimates are pragmatic and reflect the likely effect of the intervention under real-world conditions, when communities and individuals may not participate in the intervention. It also preserves the benefits of the randomized design (45).

We will estimate all treatment effects based on a contrast between a suitable summary measure of the outcome in the intervention group compared to the control group at endline, and we will use baseline outcome and covariate data to create covariate-adjusted treatment effect estimates. We treat these covariate-adjusted results as our primary evidence about the causal effects of the intervention, as they typically provide increased precision and reduce the biasing impact of any imbalances between treatment groups in terms of the distributions of potential outcomes and participant/cluster characteristics that are causally related to the endline outcomes (46). We will also produce corresponding covariate-unadjusted estimates, where appropriate, and treat those as sensitivity analyses. As recommended by the *Consort 2010 statement: extension to cluster randomized trials* (47), for all binary outcomes we will compute treatment effects on both the difference and ratio scales (both adjusted and unadjusted for covariates).

When making judgments about the likely treatment effects in the target populations of interest we will focus on treatment effect point estimates and their 95% confidence intervals (48). However, for interested readers we will also compute and present the corresponding two-sided *p*-values for those treatment effects (computed based on the null hypothesis of no difference between treatment groups). We will also present a summary measure of each outcome within each treatment group at baseline and endline based on the summary measures contrasted for the treatment effect.

##### Missing data

Based on experience of conducting similar surveys in this content, we do not expect any missing data from participants who consent to being part of either survey. However, we do expect a small proportion of eligible individuals who we approach to participate in both surveys will refuse to do so. We will record and present data on the numbers of eligible participants who were approached to participate and the numbers who agreed, so that readers can judge whether there is likely to be any substantial impact of selection bias from this process on the results.

#### Primary outcomes

##### Main analyses

As our intervention targets communities and our interest is on the community level impact of the intervention, for our two primary outcomes we will estimate cluster-average treatment effects (40). Consequently, we will analyze our two knowledge score primary outcomes using cluster-level analysis methods that are suitable for stratified, cluster-randomized, controlled trials (44, 49). This approach allows us to estimate covariate-adjusted and covariate-unadjusted cluster-average treatment effects that account for the clustered structure of the study design and data.

For our covariate-adjusted analyses for each primary outcome we will use a two-stage method that first involves creating an ordinary least-squares linear regression model with the survey participants’ percentage knowledge scores as the outcome variable and a range of individual-level and cluster-level variables as adjustment covariates (see below), including a variable identifying the strata (subdistricts), but excluding the treatment group variable. Using the model, we would then compute model-predicted outcome values for each survey participant (i.e., their predicted knowledge score percentage), based on their observed covariate values. We would then take the mean of the individual-level predicted outcome values within each cluster to create cluster-level model-predicted outcomes values. We would also take the mean of participants’ observed percentage knowledge scores within each cluster to create cluster-level observed outcome values. We would then subtract the cluster-level observed outcome values from the cluster-level model-predicted outcome values to create cluster-level difference residuals (44). In the second stage we would then estimate the (covariate-adjusted) cluster-average treatment effect via a second ordinary least-squares linear regression but with the cluster-level difference residuals as the outcome and one covariate for the clusters’ treatment group, based on the regression coefficient for the treatment group covariate along with its t-based 95% confidence intervals and two-sided *p*-value (correcting the degrees of freedom for the stratified approach) (49).

In these analyses we will adjust for the following covariates: sex (female/male), age (years) and age^2^, education level (none, less than primary, primary, less than secondary, secondary or less than higher secondary, higher secondary, graduate/post-graduate), employment status and main role in the last 30 days (no paid/in-kind work, nonprofessional/manual, personal business, professional), ownership of any animals by the household for food/economic purposes (yes/no), number of individuals living in the household, and the cluster-level baseline mean of the primary outcome being analyzed. We chose these variables as being plausibly prognostic of our outcomes.

We will also produce covariate-unadjusted cluster-average treatment effect estimates for the two primary outcomes using the same approach but excluding all covariates in the first regression model other than one identifying the strata.

We will adjust both the *p*-values and the confidence intervals for the multiple testing of the two primary outcomes via the Bonferroni approach separately for both the covariate-adjusted and covariate-unadjusted analyses.

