Based on these inputs and using the approach of (42) (based on formula 2 and assuming a cluster-level analysis), we then looked at a range of sample size scenarios. We adjusted the standard alpha level of 0.05 to 0.025, following a Bonferroni approach to account for the multiple testing of two primary outcomes. From these results we will aim to sample 44 participants per cluster (22 per village), so 1,100 participants across 25 clusters per treatment group and 2,200 participants across all 50 trial clusters, for the baseline and endline surveys. Conditional on these assumptions, when comparing between the treatment groups at endline we will have 90% power to detect a 14-percentage-point or greater difference between each group’s mean cluster-level percentage knowledge score regarding correct and appropriate knowledge about antibiotics, ABR, and usage of antibiotics for human illness, and 90% power to detect a 11-percentage-point or greater difference between each group’s mean cluster-level percentage knowledge score regarding correct and appropriate knowledge about usage of antibiotics for animal health and antibiotic-related environmental considerations.

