### Randomization

The trial statistician ([name]) will randomize all sampled clusters to the intervention or control groups in an overall 1:1 ratio using a stratified and restricted approach (44). This will involve stratifying the randomization by randomizing clusters within each subdistrict separately in a temporally staggered, subdistrict-by-subdistrict sequence (see *Trial schedule*) for logistical reasons. Within each subdistrict we will simultaneously randomize the 10 sampled study clusters within that subdistrict in a 1:1 ratio (i.e., 5 per treatment group) using a restricted approach, which aims to balance (across treatment groups) the baseline cluster-level values of the first (primary outcome) percentage knowledge score regarding correct and appropriate knowledge about antibiotics, ABR, and usage of antibiotics for human illness. Given that we are randomizing relatively few clusters, this randomization approach will increase the chances of obtaining an effective balance between treatment groups in terms of both the expected endline primary outcomes under the counterfactual that the intervention is not applied, as well as other observed and unobserved characteristics that are strongly causally related to at least the primary outcomes (44).

Specifically, using the baseline survey data for each cluster we will first compute the baseline cluster-level mean percentage knowledge score from the percentage knowledge scores of all survey participants in that cluster. Following the approach described by (44), we will then develop R code to randomize the clusters in one subdistrict at a time subject to the following restriction. For any given subdistrict the code will first enumerate every possible way the 10 clusters in the subdistrict can be allocated between the treatment groups in a 1:1 ratio. Within each subdistrict there are ^10^C_5_ = 252 possible ways to allocate the 10 clusters in a 1:1 ratio. The code will then look at each of those allocations and for each allocation it will compute the mean of the cluster-level mean percentage knowledge scores for the clusters allocated to each treatment group, and the difference between those treatment group means. Lastly, it will randomly select one of the possible allocations where the difference between the treatment group means is ≤ ± 5 percentage points (i.e., where the means of the cluster-level mean percentage knowledge scores are similar between the treatment groups at baseline).

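### The covariate-unadjusted sensitivity analysis of primary outcome 1 uses a t-test that ignores the restricted randomisation, so its interval is too wide if baseline and endline cluster means are positively correlated

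*Protocol article*

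**What the plan says.** **Allocation** (Protocol article, Randomization). Each of five subdistricts has 10 clusters, split 5:5. For each of the 252 possible splits, the code compares the arms' means of the baseline cluster-level knowledge score 1. It will then "randomly select one of the possible allocations where the difference between the treatment group means is" no more than 5 percentage points. The limit is widened in 5-point steps if fewer than half of the 252 splits qualify, or if a pair of clusters falls in the same arm too often.

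**Analysis** (Main analyses). Stage one regresses individual scores on covariates and strata. Stage two regresses the cluster residuals on arm and reports the coefficient "along with its t-based 95% confidence intervals and two-sided" p-value, "correcting the degrees of freedom for the stratified approach". The adjusted version includes the cluster-level baseline mean of the outcome being analysed. The unadjusted version is obtained "using the same approach but excluding all covariates in the first regression model other than one identifying the strata".

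**Roles** (Outcome treatment effects). The adjusted results are the primary evidence. For the others: "We will also produce corresponding covariate-unadjusted estimates, where appropriate, and treat those as sensitivity analyses". Main analyses applies the Bonferroni correction to the p-values and intervals of both sets.

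**The concern.** The strata-only t-test takes its standard error from the spread of cluster values within subdistricts. That is the right yardstick if any 5:5 split could have been drawn. Here the splits with large baseline imbalance were excluded in advance. If the baseline score predicts the endline score, excluding them reduces how much the arm difference varies from one admissible allocation to another, but leaves the within-subdistrict spread of cluster values unchanged. The reported standard error is then larger than the true one.

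At stake is how the sensitivity analysis reads beside the main result. Part of any gap in precision between the adjusted and unadjusted results would come from a miscalibrated test and not from the value of adjustment. A reader could mistake that for fragility of the finding.

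**Working it through.** **Inputs from the protocol (Sample size; Randomization):** 25 clusters per arm, 44 participants per cluster, ICC 0.3, overall variance 40 for outcome 1, 5 strata of 10 clusters, and the restriction rule above. On alpha: "We adjusted the standard alpha level of 0.05 to 0.025, following a Bonferroni approach".

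**Assumed, because the protocol gives no figure:** the cluster autocorrelation (CAC), meaning the correlation between true baseline and endline cluster means. It was varied from 0 to 1. The degrees of freedom were taken as 50 - 2 - 4 = 44.

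**1. The plan's own figure.** A variance of 40 reproduces the stated power only as a count out of 25 questions.
- SD = √40/25 = 25.3 points, variance 640.
- Cluster-mean variance = 640 × (0.3 + 0.7/44) = 202.2, SD 14.22.
- SE of the arm difference = √(2 × 14.22²/25) = 4.02.
- Detectable difference = 4.02 × (2.241 + 1.282) = 14.2 points.

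This agrees with "we will have 90% power to detect a 14-percentage-point or greater difference". The 4.02 is also the standard error that the strata-only t-test will report on average.

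**2. Observed correlation.** The reliability of a cluster mean is 0.3/(0.3 + 0.7/44) = 0.95, so r = 0.95 × CAC.

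**3. Simulation under no effect** (ICC 0.3, 4,000 trials per row, all 252 splits enumerated per subdistrict, both relaxation rules applied):

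| CAC | r | Mean model SE | True SD | Ratio | Type I error at 0.025 |
|---|---|---|---|---|---|
| 0 | 0 | 3.99 | 4.14 | 0.97 | 2.8% |
| 0.3 | 0.28 | 4.01 | 3.92 | 1.02 | 2.0% |
| 0.5 | 0.47 | 4.00 | 3.77 | 1.06 | 1.4% |
| 0.8 | 0.76 | 4.01 | 3.15 | 1.28 | 0.45% |
| 1.0 | 0.95 | 4.03 | 2.54 | 1.59 | 0.05% |

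Separate runs gave 1.9% at CAC 0.5 and 0.5-0.6% at CAC 0.8. Without the restriction, CAC 0.8 gives 2.3% and a ratio of 0.99, so the restriction is the cause. The 5-point limit survived in only about 21% of subdistricts and about 77% moved to 10 points. On average 67% of splits stayed available.

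**4. Consistency check.** If the restriction removes a share q of the variance of the baseline arm difference, the endline variance shrinks by the factor 1 - r²q.
- From the last row: (2.54/4.02)² = 0.40, so q = 0.60/0.95² = 0.66.
- At r = 0.76: 1/√(1 - 0.58 × 0.66) = 1.27.
- At r = 0.47: 1/√(1 - 0.22 × 0.66) = 1.08.

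At CAC 0.5 the inflation is therefore about 8%. The single run above gave 6%, and others gave 8-10%.

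**5. Lower ICC.** Type I error at 0.025 is 0.55% with ICC 0.1 and r = 0.66, 1.6% with ICC 0.05 and r = 0.56, and 1.8% with ICC 0.02 and r = 0.47 (the maximum possible there).

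**6. Power at alpha 0.025,** planned t-test against a permutation test of the same unadjusted difference over the admissible splits (ICC 0.3, 1,500 trials):

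| CAC | Effect (points) | t-test | Permutation | Loss |
|---|---|---|---|---|
| 0.8 | 8 | 34.1% | 57.3% | 23.2 |
| 0.8 | 10 | 57.3% | 78.8% | 21.5 |
| 0.8 | 12 | 78.7% | 91.5% | 12.8 |
| 0.8 | 14 | 92.1% | 97.7% | 5.6 |
| 0.8 | 15 | 95.9% | 98.5% | 2.6 |
| 0.5 | 14 | 89.2% | 91.7% | 2.5 |
| 0.3 | 14 | 87.0% | 86.9% | none |

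**7. With the balancing score in the model** (baseline cluster mean added, 43 degrees of freedom), type I error is 1.7-3.0% at nominal 2.5% and the SE ratio 0.97-1.02 in every scenario.

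**The case against.** **It is only a sensitivity analysis, and the error is cautious.** This stands. The adjusted results are the primary evidence, and for outcome 1 they contain the balancing score. A reader might infer that the trial's main conclusion is compromised. It is not: the unadjusted estimate is not biased and no false positives are created.

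**The test need not be very conservative.** This also stands. A reader might infer severe conservatism from the restriction alone, but that requires a high correlation (r of about 0.66 or more in these runs). The protocol reports none, calls its ICC conservative, surveys different people at endline with a separately formed field team, and finishes well over a year after baseline. On the other side, Randomization justifies the restriction by its expected effect on endline outcomes, and Main analyses calls the baseline cluster mean plausibly prognostic. If that reasoning is right, r is above zero and the test is miscalibrated to some degree.

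**Little power is lost at the target effect.** True at 14-15 points. The large losses arise only for smaller effects with high stability, and the protocol rests its judgements on estimates and intervals more than on p-values. The width of the interval, however, is wrong whatever the effect.

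**The analysis plan could settle this.** It could, but the article does not leave the matter open: it fixes both the covariate set and the only correction.

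**Adding the baseline score would remove the covariate-free check.** A fair objection to that remedy, which the permutation test avoids.

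**Conclusion.** The point holds for the covariate-unadjusted sensitivity analysis of primary outcome 1. As written, its interval and p-value ignore the restriction and are conservative whenever baseline and endline cluster means are positively correlated. At ICC 0.3 the standard error is about right at CAC 0, about 6-10% too large at 0.5 and 25-28% too large at 0.8. The CAC is an assumption throughout, so the size is a range and no single figure can be claimed.

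A reader might extend the finding to outcome 2 and to the whole-sample secondary outcomes, which reuse the method. The documents do not support a size there. Allocation was restricted on score 1 alone, so the effect depends on how well baseline score 1 predicts each of those outcomes, and this was not quantified. The change is worth making because it is cheap, but no primary conclusion depends on it.

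**What to change.** In Main analyses, keep the unadjusted arm difference but take its p-value from a permutation test. Re-draw allocations within each subdistrict only from the splits that met the restriction, using the limit actually applied there after any widening. Obtain the interval by inverting that test at the Bonferroni-adjusted level. The randomisation code already enumerates these splits, so the cost is a sentence in the analysis plan, a few lines of R and some computing time. No new data are needed.

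Alternatively, keep the cluster-level baseline mean of knowledge score 1 alongside strata in stage one and call the analysis minimally adjusted. This is simpler and restores close to nominal size for outcome 1, but the analysis is then no longer strictly unadjusted.
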